## **7 DEFINITION OF END OF TRIAL**

This is a non-CTIMP study with all eligible patients recruited consecutively into the study and undergoing each study procedure. Recruitment will be terminated once 375 patients have been recruited and undergone a DCE-CT scan.

The study has two possible endpoints for each patient:

**Either** the diagnosis of lung cancer via biopsy **or** a diagnosis of benign or non- lung cancer via either biopsy (please note that in this case economic data collection will continue to be required for 2 years follow up)

**Or** failure of the imaged nodule to progress (increase in size) during the 2 year follow up period.

The end of the study will be reached when the last study patient reaches two years of follow up or withdraws full consent for continuing in the study.

**PLEASE NOTE:** *Health Resource Data will be collected for all patients over a 2 year period following the DCE-CT scan, therefore the end of study form will not be completed until this time unless patients have withdrawn full consent.*

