### 3.1 TRIAL OUTCOME MEASURES

Primary outcome measures will include diagnostic test characteristics (sensitivity, specificity, accuracy) for FDG-PET/CT and DCE-CT in relation to a subsequent clinical diagnosis of lung cancer. The outcome measures used in the economic model will include accuracy, estimated life expectancy, and quality adjusted life years (QALYs). Costs will be estimated from an NHS perspective. Incremental cost-effectiveness ratios will compare management strategies with DCE-CT to strategies without DCE-CT.

Secondary outcome measures will include diagnostic test characteristics for FDG-PET/CT with incorporation of CT appearances and combined DCE-CT/FDG-PET/CT. The incidence of incidental extra-thoracic findings on FDG-PET/CT, subsequent investigations and costs will also be determined.

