## **4.3 EXCLUSION CRITERIA**

- Pregnancy
- History of malignancy within the past 2 years
- Confirmed aetiology of the nodule at the time of qualifying CT scan – As this is a diagnostic study, should the aetiology of the nodule be confirmed by investigation such as FDG-PET/CT or bronchoscopy prior to consent the patient remains eligible as the intention to include is made on the analysis of the qualifying CT scan.
- Biopsy of nodule before DCE-CT scan
- Contra-indication to potential radiotherapy or surgery
- Contra indication to scans (assessed by local practice)

All patients meeting inclusion criteria and none of the exclusion criteria will be eligible and recruited consecutively into the study. In giving consent they will be expected to follow the procedures described below

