## **8.4 REFERENCE STANDARD**

The reference standard will comprise pathological and/or imaging follow up data at 24 months as used widely in previous assessments of diagnostic performance in the characterisation of SPNs. (To restrict the reference standard to biopsy material would not be appropriate on grounds of ethics or bias. Ethical concerns would prevent biopsy of all SPNs, including those benign on imaging. Bias would be introduced if a clinically indicated biopsy were an inclusion criterion because the sample would not be representative of all patients with SPN.)

All patients without definitive pathological findings will undergo repeat CT examinations of the chest at 3, 9 and 24 months. Biopsy of lesions increasing in size during the follow up period will be performed if considered necessary on clinical grounds by the local care team.

Lesions showing a less than 20% increase in size during follow up will be considered benign. (This criterion is based on the reported doubling times of pulmonary malignancies which can be as long as 465 days, equivalent to a 20% increase in tumour diameter at 2 years [25].)

The patient's clinical notes will also be reviewed at 24 months to determine how the patient has been managed after imaging and to confirm that decision tree models accurately reflect clinical practice (e.g. proportion of patients with imaging positive for malignancy undergoing fine-needle biopsy or surgical excision).

Clinical information will be extracted using a standardised data collection form including information relating to costs, such as investigative procedures received, surgical interventions, inpatient stays etc, and used to inform subsequent economic analyses.

The follow-up investigations and outcomes for incidental extra-thoracic findings on FDG-PET/CT and DCE-CT will also be determined (secondary aim 3).

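### The growth rule for benign does not require an untreated nodule, so a nodule treated as cancer without histology that then fails to grow is counted benign

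*Protocol*

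**What the plan says.** Protocol section 7: "The study has two possible endpoints for each patient". The first is "the diagnosis of lung cancer via biopsy", or a benign or other non-lung-cancer diagnosis by biopsy. The second is "failure of the imaged nodule to progress (increase in size) during the 2 year follow up period".

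Section 8.4: "The reference standard will comprise pathological and/or imaging follow up data at 24 months". Patients without conclusive pathology are to have repeat chest CT at 3, 9 and 24 months. Then: "Lesions showing a less than 20% increase in size during follow up will be considered benign". No condition on intervening treatment is attached. Biopsy of a growing lesion "will be performed if considered necessary on clinical grounds by the local care team", and no class is given to a lesion that grows by 20% or more and is not biopsied.

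Section 3.1 relates the accuracy measures to "a subsequent clinical diagnosis of lung cancer", and section 8.6 and the synopsis do the same. None of them defines the term. Section 9.1 limits the accuracy analysis to patients whose lung cancer status at 2 years is known.

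Several places leave room for treatment without tissue:

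- The schedule footnotes say that visits 2 and 3 may be biopsy or treatment visits when the scans suggest cancer.
- Section 1.1 cites guidance that places PET where tissue cannot be obtained.
- Section 5.2 expects biopsy in many cases, not in all.
- Section 8.4 plans to find out what proportion of imaging-positive patients had a needle biopsy or excision.

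**The concern.** Lack of growth points to a benign nodule only while the nodule is left alone. Once a nodule has been treated, lack of growth may reflect the treatment, and the rule in section 8.4 does not separate the two cases. Section 7 does not rescue such a patient, because its only route to a lung cancer endpoint is biopsy. Section 3.1, taken at its word, would call the same patient a cancer. Two people applying different sections could therefore give one patient opposite labels.

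A patient treated without tissue will usually have been treated because the imaging was positive. Labelled benign, that patient becomes a false positive for the index tests, and does so in the smaller group: the plan expects 118 benign nodules against 257 malignant. The resulting accuracy and prevalence figures feed the economic model. A larger sample would not remove this error.

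**Working it through.** **Plan's own figures (section 9.1).** N = 375 and prevalence 68.5%: 375 × 0.685 = 256.9, so 257 malignant and 118 benign. Half-width = 1.96 × √(p(1−p)/n):

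- PET specificity: 1.96 × √(0.90 × 0.10 / 118) = 5.41 points (stated 5.4).
- DCE-CT specificity: 1.96 × √(0.83 × 0.17 / 118) = 6.78 points (stated 6.8).
- Sensitivities with n = 257: 3.32 points for PET and 4.11 for DCE-CT (stated 3.3 and 4.1).

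All reproduce. The issue is classification, not sample size.

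**Treated cancers counted benign.** Let k be the number of true cancers treated without histology that then fail to grow. The documents give no k; 2%, 5% and 10% of 257 are used here, that is 5, 13 and 26. Take all k as PET positive. True negatives stay at 0.90 × 118 = 106.2, and true positives start at 0.92 × 257 = 236.44.

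| k | PET specificity, 106.2/(118+k) | Prevalence, (257−k)/375 | PET sensitivity, (236.44−k)/(257−k) |
|---|---|---|---|
| 0 | 90.0% | 68.5% | 92.0% |
| 5 | 106.2/123 = 86.3% | 252/375 = 67.2% | 91.8% |
| 13 | 106.2/131 = 81.1% | 244/375 = 65.1% | 91.6% |
| 26 | 106.2/144 = 73.8% | 231/375 = 61.6% | 91.1% |

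Sensitivity hardly moves; specificity and prevalence carry the bias.

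**When the shift exceeds the stated precision.**

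- PET, all k positive: k = 7 gives 106.2/125 = 85.0% (shift 5.0 points); k = 8 gives 106.2/126 = 84.3% (shift 5.7).
- PET, 92% of k positive: k = 9 gives (106.2 + 0.08 × 9)/127 = 84.2% (shift 5.8).
- So 8 to 9 patients, or 8/257 = 3.1% to 9/257 = 3.5% of expected malignancies.
- DCE-CT has 0.83 × 118 = 97.94 true negatives. All k positive: k = 11 gives 97.94/129 = 75.9% (shift 7.1). With 87% positive: k = 13 gives (97.94 + 0.13 × 13)/131 = 76.1% (shift 6.9).

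**Growing nodules without biopsy.** The two sections side by side:

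| Growth, no biopsy | Section 7 | Section 8.4 |
|---|---|---|
| None | endpoint met | benign |
| Above 0, below 20% | endpoint not met (size increased) | benign |
| 20% or more | endpoint not met | no class stated |

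Suppose 10 unclassified growers drop out of the analysis:

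- 10 malignant, all PET negative: sensitivity 236.44/247 = 95.7%. All PET positive: 226.44/247 = 91.7%. Prevalence 247/365 = 67.7% either way.
- 10 benign, half PET positive: specificity 1 − (11.8 − 5)/108 = 93.7%, prevalence 257/365 = 70.4%.

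The direction depends on who these patients are.

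**The case against.** The best defence is that the growth rule was never meant for treated patients. It follows the sentence on repeat CT. The schedule footnotes keep the follow-up visits for patients whose nodule still has no diagnosis, and section 5.2 ties the 3, 9 and 24 month scans to surveillance. A patient treated as having cancer would then lie outside the rule. This is a fair reading, but section 8.4 sends every patient without conclusive pathology to repeat CT. Even on the milder reading, section 7 gives the treated patient no route to a lung cancer endpoint.

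A reader might also infer from the exclusion "Contra-indication to potential radiotherapy or surgery" that the plan expects radiotherapy without histology. It does not say so. It only requires that such treatment be possible, and section 5.2 links cancer management to cases already shown to be cancer. The other places cited leave room for treatment without tissue, but none says that it happens or how often.

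For growing nodules, section 8.4 allows imaging alone to classify, and its 20% limit is justified by the growth of malignancies, so 20% or more is by implication not benign. Section 9.1 could also be taken to exclude patients whose status is unresolved. Both are inferences: the class is not written down, and the only example of exclusion in section 9.1 is drop-out before 2 years.

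Finally, clinical diagnosis may be a loose outcome label that section 8.4 makes operational. If so, section 8.4 has done it with a rule that can reverse the label. This is not a detail left to an analysis plan, since the protocol itself fixes the reference standard and the endpoints.

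**Conclusion.** The point holds in conditional form. As written, sections 7 and 8.4 would label as benign a nodule that was treated as cancer without histology and then did not grow, contrary to sections 3.1 and 8.6. If such patients occur and are test positive, specificity and prevalence are biased downwards, and about 8 to 9 of them (roughly 3% of expected malignancies) shift PET specificity by more than its planned half-width. With 5 patients the shift of 3.7 points stays inside it; with none it is zero. The number, and its near-complete test positivity, are assumptions.

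A reader might infer that the trial's specificity will be biased. The documents do not support that without a count of treated patients. A reader might also infer that losing unbiopsied growers flatters sensitivity and NPV. That holds only if they are mainly test-negative cancers; as shown above, other mixes move the estimates differently. What is certain is that growth of 20% or more without biopsy has no stated class, and that sections 7 and 8.4 disagree on growth between 0 and 20%.

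**What to change.** Reconcile sections 3.1, 7, 8.4 and 9.1 (and 8.6, which repeats the wording of 3.1). Specifically:

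- State that growth below 20% defines benign only for nodules that received no anticancer treatment during follow-up, and align section 7 with section 8.4 on growth between 0 and 20%.
- Record two separate reference categories that are never benign by default: treated as malignant without pathology, and grew by 20% or more without pathology.
- Prespecify one primary handling, for example exclusion, or classification by a clinical diagnosis made, where possible, without reference to the index test results.
- Report sensitivity analyses that class these patients all malignant, exclude them, and class them all benign.

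Classing both groups as cancer in the primary analysis is tempting but is a trade-off. The MDT directs management after both scans, so those positives would be correct by construction. If 5 of the treated patients were in fact benign and PET positive, specificity would rise from 90% to 106.2/113 = 94.0%.

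The cost is protocol wording, one field on the end-of-study form and some extra analysis; management data are already extracted at 24 months. The price is a possible small loss of patients or some incorporation bias, which the sensitivity analyses would show. The change concerns classification for analysis only and does not alter who is biopsied or treated.

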## 8 ASSESSMENT AND ANALYSIS

### 8.1 ASSESSMENT OF DIAGNOSTIC ACCURACY OF FDG-PET/CT

Analysis will be both qualitative and quantitative.

#### Qualitative analysis

FDG-PET images and attenuation correction CT images will be classified according to a five-point scale using the guidelines in table 1.

An audit of the consistency of qualitative analysis will comprise of a central second reading of 10% of FDG-PET/CT scans .

#### Quantitative analysis

Scans will be analysed and interpreted by PET-CT specialists at each centre.

Quantitative analysis of FDG-PET/CT data will consist of measurements of FDG uptake expressed as the maximum standardised uptake value (SUVmax).

The presence of incidental extra-thoracic findings on PET and maximal tumour diameter as measured by CT will be recorded.

The diagnostic performance of FDG-PET will be assessed with and without incorporation of the CT appearances using the guidelines in table 1 (secondary aim 1).

Based on previous studies [19, 20], the combined FDG-PET/CT assessment will be classified as positive for malignancy if one of the following criteria are met;

- grade 4 on FDG-PET,
- At least grade 3 on both modalities
- Grade 2 on PET and grade 3 or 4 on CT.

| Grade | Significance                 | FDG-PET                      | Attenuation Correction CT                                   |
|--------------|-------------------------------------|--------------------------------------------------|--------------------------------------------------------------------|
| 0            | No evidence of malignancy           | No visible uptake                                | Round, well defined lesion with laminated or popcorn calcification |
| 1            | Low probability of malignancy       | Uptake less than mediastinal blood pool          | Inflammatory features e.g. air bronchograms, enfolded lung         |
| 2            | Indeterminate                       | Uptake comparable to mediastinal blood pool      | Smooth well defined margins, uniform density                       |
| 3            | High probability of malignancy      | Uptake greater than mediastinal blood pool       | Lobulated, spiculated or irregular margins                         |
| 4            | Very high probability of malignancy | Evidence of distant metastases (i.e. M1 disease) | Evidence of distant metastases (i.e. M1 disease)                   |

Table 1: Guidelines for the interpretation of FDG-PET and Conventional CT

## **8.2 ASSESSMENT OF DIAGNOSTIC ACCURACY OF DCE-CT:**

DCE-CT will be performed immediately after or within a maximum of 21 days either side of the clinically indicated PET/CT examination. Please note scans should ideally be performed within 14 days .

Interpretation of DCE-CT will comprise quantitative analysis performed by specialists at each participating site with central review for quality assurance. Quantitative analysis of DCE-CT data will consist of measurements of contrast enhancement.

## **8.3 ASSESSMENT OF DIAGNOSTIC ACCURACY OF COMBINED FDG-PET AND DCE-CT:**

Novel diagnostic criteria for combined FDG-PET and DCE-CT will be developed (secondary aim 2) including quantitative values such as SUVmax/peak enhancement, SUVmax/SPV etc.

The accuracy of combined diagnostic criteria will be evaluated.

## **8.4 REFERENCE STANDARD**

The reference standard will comprise pathological and/or imaging follow up data at 24 months as used widely in previous assessments of diagnostic performance in the characterisation of SPNs. (To restrict the reference standard to biopsy material would not be appropriate on grounds of ethics or bias. Ethical concerns would prevent biopsy of all SPNs, including those benign on imaging. Bias would be introduced if a clinically indicated biopsy were an inclusion criterion because the sample would not be representative of all patients with SPN.)

All patients without definitive pathological findings will undergo repeat CT examinations of the chest at 3, 9 and 24 months. Biopsy of lesions increasing in size during the follow up period will be performed if considered necessary on clinical grounds by the local care team.

Lesions showing a less than 20% increase in size during follow up will be considered benign. (This criterion is based on the reported doubling times of pulmonary malignancies which can be as long as 465 days, equivalent to a 20% increase in tumour diameter at 2 years [25].)

The patient's clinical notes will also be reviewed at 24 months to determine how the patient has been managed after imaging and to confirm that decision tree models accurately reflect clinical practice (e.g. proportion of patients with imaging positive for malignancy undergoing fine-needle biopsy or surgical excision).

Clinical information will be extracted using a standardised data collection form including information relating to costs, such as investigative procedures received, surgical interventions, inpatient stays etc, and used to inform subsequent economic analyses.

The follow-up investigations and outcomes for incidental extra-thoracic findings on FDG-PET/CT and DCE-CT will also be determined (secondary aim 3).

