### 5.2 PATIENT MANAGEMENT FOLLOWING PET-CT AND DCE-CT

Following the PET-CT and DCE-CT investigations, management of the SPN should be directed by the local/specialist lung MDT.

In many cases nodule biopsy or excision biopsy may be undertaken. Those cases shown to be due to lung cancer (or other malignancy) will be managed according to local protocols. Follow up/outcome data will be collected by CRF.

In some cases it is recognised that nodule surveillance is appropriate (with or without prior biopsy). In these cases it is recommended that follow up is performed at

- 3 months
- 9 months
- 24 months

as per Fleischner Society Guidelines (Radiology 2005;237:395) for management of indeterminate nodules >8mm. (Deviation from these time points based on clinical need is at the discretion of the MDT)

At each visit the following should be performed:

- Chest CT (low dose, thin section, unenhanced) unless MDT feels it is inappropriate
- Recording of any biopsy samples taken

- Recording of health resource use information

At 2 years

- Health resource data will be collected from patient records
- The end of study CRF will be completed in the InForm Database
- The PI will sign off the patients electronic CRF record and the database will be locked for that patient

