### **5.4 ACCESS TO OUTCOME DATA**

If patients are lost to follow up within 2 years (e.g. relocation to another health authority) outcome data will be obtained via the Health and Social Care Information Centre. Consent for this will be taken during initial consenting process.

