### Statistical analysis

#### (i) Diagnostic accuracy for 2 year follow-up

We will consider the diagnostic accuracy of positive FDG-PET and DCE-CT, both separately and in conjunction, in relation to a diagnosis of lung cancer by 2 years. In these analyses we will only be able to use those patients for whom the presence of lung cancer by 2 years is known; i.e. those without diagnosed lung cancer who drop-out before the end of 2 years will be excluded. This is likely to be small.

Initially, the separate diagnostic performance of FDG-PET/CT and DCE-CT will be examined using diagnostic criteria defined and over the full range of possible threshold values. At each threshold sensitivity and specificity will be estimated (with 95% confidence intervals), and the Receiver Operator Characteristic (ROC) curve will be calculated. The optimal cut-point from the range of values will be reported based on keeping the sensitivity above 90% and maximising specificity within this limitation. An alternative cut-point that provides the best trade off in sensitivity and specificity will also be reported. The sensitivity, specificity, positive predictive value (PPV) and negative predictive value (NPV) at these cut-points will then be presented with 95% confidence intervals. When translating sensitivity and specificity to PPV and NPV, we will need to assume a particular prevalence. This will be based on the prevalence in our study, and also we will report PPV and NPV for a range of other prevalence's reported in the literature (identified from our systematic review).

Secondly, the diagnostic performance of FDG-PET/CT and DCE-CT combined will also be examined using the same techniques as above; we will class patients as 'positive' if they have both FDG-PET and DCE-CT positive, and all others as 'negative'. Again, a range of different thresholds for both FDG and DCE will be considered.

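### The benign-by-stability label relies on a 24-month CT that section 5.2 makes optional, and the benign rule in section 8.4 does not itself require that CT

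*Protocol*

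**What the plan says.** Section 8.4 of the protocol sets the time point: "The reference standard will comprise pathological and/or imaging follow up data at 24 months". For surveillance it is unconditional: "All patients without definitive pathological findings will undergo repeat CT examinations of the chest at 3, 9 and 24 months". The imaging rule follows: "Lesions showing a less than 20% increase in size during follow up will be considered benign". Its stated basis is that doubling times "can be as long as 465 days, equivalent to a 20% increase in tumour diameter at 2 years".

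Section 5.2 treats the same schedule as a recommendation. It adds "Deviation from these time points based on clinical need is at the discretion of the MDT", and lists for each visit "Chest CT (low dose, thin section, unenhanced) unless MDT feels it is inappropriate". The schedule of observations allows local practice to replace the 3- and 9-month visits, but not the 24-month visit.

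Section 9.1, analysis (i), uses only patients whose 2-year lung cancer status is known, and says "those without diagnosed lung cancer who drop-out before the end of 2 years will be excluded". Section 8.4 has the clinical notes of patients reviewed at 24 months. For patients lost to follow-up, section 5.4 says "outcome data will be obtained via the Health and Social Care Information Centre".

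**The concern.** Section 8.4 assumes a 24-month scan that section 5.2 does not guarantee, and the rule that turns stability into a benign label does not mention that scan. A patient whose last CT was at 3 or 9 months, and whose notes are reviewed at 24 months, has stayed in the study. Nothing in section 9.1 clearly removes this patient, and the wording of the 8.4 rule is met. Section 5.4 does not say whether the absence of a cancer record counts as benign.

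The MDT decides on scanning after both index tests, and section 8.6 says that test results drive management. Early stopping may therefore be commoner after negative tests. A missed slow-growing cancer would then move from false negative to true negative. Sensitivity is part of the primary outcome. NPV bears on the idea, in the background on combined DCE-CT/PET, that two benign results might reduce the need for surveillance.

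**Working it through.** **1. The protocol's own growth figure.** For a volume doubling time DT, the diameter ratio after T days is 2^(T/(3·DT)). With DT = 465 and T = 730 this is 2^(730/1395) = 1.437, a 43.7% increase, not 20%. Growth of 20% is reached at about day 367. This discrepancy is a separate matter, and the point here does not depend on it.

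**2. What a fixed 20% means at each scan time.** A 20% diameter increase needs 3·log2(1.2) = 0.789 doubling times. The rule therefore misses any DT above T/0.789.

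| Last CT | Rule misses DT above | Diameter growth at DT 465 | Growth on the protocol's equivalence, 1.2^(T/730) − 1 |
|---|---|---|---|
| 3 months (91 d) | 115 d | 4.6% | 2.3% |
| 9 months (274 d) | 347 d | 14.6% | 7.1% |
| 24 months (730 d) | 925 d | 43.7% | 20.0% |

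A cancer at the protocol's 465-day limit is below 20% at 3 and 9 months on either conversion. The rule does not define size, but the 8.4 rationale speaks of diameter. If size meant volume, the limits would be 346 days at 3 months and 1,042 days at 9 months. The 465-day cancer (14.5% and 50.4% volume growth) would then be missed only at 3 months. The rule's meaning still depends on the interval.

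**3. Effect on PET accuracy if the missed cancers are test-negative.** Inputs from section 9.1 are 257 malignant and 118 benign nodules, with PET sensitivity 92% and specificity 90%. The planned half-width reproduces: 1.96·√(0.92·0.08/257) = 3.3 points. Expected counts are TP 236.4, FN 20.6, TN 106.2 and FP 11.8.

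The protocol gives no number of mislabelled cancers, so 5 and 10 are assumed. They are 24% and 49% of the expected false negatives.
- Sensitivity: 236.4/(257 − 5) = 93.8%; 236.4/(257 − 10) = 95.7%.
- NPV as planned: 106.2/(106.2 + 20.6) = 83.8%. With 5 moved: 111.2/126.8 = 87.7%. With 10 moved: 116.2/126.8 = 91.7%.

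**4. Other patterns of missed cancers.**
- 10% of all cancers missed whatever the result: PET sensitivity stays at 92.0% and specificity falls to (106.2 + 2.1)/(118 + 25.7) = 75.3%. DCE-CT sensitivity stays at 87.0% and its specificity falls from 83% to 70.5%.
- Test-positive cancers missed more often (25% of TP, 5% of FN): sensitivity falls to 90.1% for PET and 84.1% for DCE-CT.

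**5. Does exclusion alone repair it?** No. Excluding the 5 or 10 cancers gives the same sensitivities, 93.8% and 95.7%, because they leave the denominator either way. With no benign patient excluded, NPV is 106.2/121.8 = 87.2% or 106.2/116.8 = 91.0%, still too high. If 30 PET-negative benign patients are also excluded (assumed), specificity becomes 76.2/88 = 86.6% instead of 90%.

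**The case against.** The strongest objection is that the protocol has a two-year anchor in several places. Section 8.4 sets the reference standard at 24 months and ties the 20% to growth at 2 years. Section 7 defines the stability endpoint over the 2-year follow-up. The schedule places a chest CT at 24 months for undiagnosed patients, and section 9.1 requires 2-year status to be known. A reader might infer from the bare benign rule that no follow-up interval is set at all, or that every patient with an early last CT is scored benign. The documents support neither. The gap is limited to patients retained to 24 months without a CT at that time, and for them the label is possible, not prescribed. Cancers diagnosed within 2 years still count as cancer, and fast growers cross 20% by 9 months.

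A reader might also infer that sensitivity is necessarily inflated. That needs the missed cancers to be mainly test-negative, which is plausible from section 8.6 but not established. The assumed 5 cases shift PET sensitivity by 1.8 points, inside the planned ±3.3.

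The MDT's latitude is legitimate in an observational study, and omitting a CT after a nodule has resolved causes no mislabelling. Handling of missing scans could also be detailed in an analysis plan that is not shown. However, the definition of the reference standard, and its conflict with section 5.2, belong to the protocol, because sites and the CRF work from it.

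**Conclusion.** The point holds in a limited form. Sections 5.2 and 8.4 conflict, and the benign rule does not require the scan on which its meaning depends. A retained patient last scanned at 3 or 9 months can be labelled benign when the scan could not have excluded a cancer with a doubling time above about 115 or 347 days. These limits assume exponential volume growth and size read as diameter.

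The result is a reference standard open to bias whose direction is not fixed by the documents. If mislabelling falls mainly on test-negative cancers, PET sensitivity is overstated by 1.8 to 3.7 points and NPV by 3.9 to 7.9 points for 5 to 10 cases. If mislabelling is unrelated to the test result, the loss is in specificity. The number of patients affected cannot be derived from the protocol, so these figures are illustrations. The change should be made, because it is cheap and concerns a primary outcome.

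**What to change.** Reconcile section 5.2 with section 8.4, leaving the surveillance schedule to the MDT. The rest concerns classification and analysis only:

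- In 8.4, state that benign by stability requires a CT at about 24 months, within a window set by the sponsor, or documented resolution of the nodule. Without either, and without pathology or a cancer diagnosis, code the reference standard as not verified. Do not treat absence of a cancer record as benign.
- Record the date of the last CT on the end-of-study CRF.
- In analysis (ii), censor these patients at the last CT.
- In analysis (i), accompany the complete-case table with a verification-bias-corrected estimate, such as Begg-Greenes or multiple imputation given both test results. These methods assume that, given what is conditioned on, verification does not depend on true status. Best- and worst-case bounds should therefore be shown too.
- Report benign calls by basis: pathology, 24-month CT, resolution, other.

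The cost is a few sentences, one CRF date and a little extra analysis, with no added scan. The downside is fewer verified benign cases and somewhat wider intervals.

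### The 20% growth limit for calling a nodule benign rests on a wrong conversion: a 465-day doubling time gives about 44% diameter growth at 2 years, and 20% at about 1 year

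*Protocol*

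**What the plan says.** Protocol section 8.4 sets the horizon: "The reference standard will comprise pathological and/or imaging follow up data at 24 months". It then gives the imaging schedule: "All patients without definitive pathological findings will undergo repeat CT examinations of the chest at 3, 9 and 24 months". The classification rule is "Lesions showing a less than 20% increase in size during follow up will be considered benign". The only reason offered for 20% is the parenthesis that follows, which refers to "doubling times of pulmonary malignancies which can be as long as 465 days, equivalent to a 20% increase in tumour diameter at 2 years".

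The rule speaks of size, while its rationale speaks of diameter. The section leaves biopsy of growing lesions to the local team and does not say how a nodule that grows by 20% or more without biopsy is to be classified.

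Two other places bear on the rule. Section 5.2 recommends follow-up at 3, 9 and 24 months but adds "Deviation from these time points based on clinical need is at the discretion of the MDT", and allows the chest CT to be left out if the MDT thinks it inappropriate. Section 7 describes the imaging endpoint as "failure of the imaged nodule to progress (increase in size) during the 2 year follow up period", with no 20% tolerance.

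**The concern.** Sensitivity and specificity against this reference standard are the primary outcome (section 3.1). The 20% rule decides the benign label for nodules without pathology, so it acts mainly on the benign group, from which specificity is estimated. Section 9.1 expects only about 118 benign nodules. One nodule is then 1/118 = 0.85% of the specificity denominator, against planned half-widths of 5.4 points (PET) and 6.8 points (DCE-CT).

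If the stated link between doubling time and growth is false, the limit does not have the meaning the protocol gives it. Because the rule names no interval, the direction of the discrepancy also depends on when the last CT was done.

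**Working it through.** **Inputs**, all from section 8.4: doubling time 465 days; stated growth 20% in diameter; stated horizon 2 years (730 days); scheduled CTs at 3, 9 and 24 months. The protocol does not say whether the doubling time refers to volume or diameter. Volume doubling of a sphere is assumed first, and the alternatives are checked below.

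**Formula.** Volume ratio = 2^(t/465). Diameter is the cube root, so diameter growth = 2^(t/(3 × 465)) − 1 = 2^(t/1395) − 1.

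**Attempt to reproduce the plan's figure.** At t = 730 the number of doublings is 730/465 = 1.57, the volume ratio is 2^1.57 = 2.97, and the diameter ratio is 2.97^(1/3) = 1.437. That is +43.7%, not +20%.

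**Other readings at 730 days:**
- linear volume growth: (1 + 730/465)^(1/3) − 1 = +37.0%
- area doubling: 2^(730/930) − 1 = +72.3%
- diameter doubling: 2^(730/465) − 1 = +196.9%

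None gives 20%.

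**Where 20% does arise.** At t = 365, 2^(365/1395) − 1 = +19.9%. Solving for +20%: t = 1395 × log2(1.2) = 367 days. The protocol's figure matches the 1-year value stated as a 2-year value.

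**Growth of a 465-day tumour at the CT times:**

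| Last CT | Days | Diameter growth | Against the 20% limit |
|---|---|---|---|
| 3 months | 91 | +4.6% | below |
| 9 months | 274 | +14.6% | below |
| 12 months | 365 | +19.9% | about equal |
| 24 months | 730 | +43.7% | above |

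**What 20% at 24 months means.** Doubling time = 730 × ln 2 / (3 × ln 1.2) = 925 days. If size were taken as volume, it would be 730 × ln 2 / ln 1.2 = 2775 days, so the dimension matters.

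**In millimetres.** For a 10 mm nodule, the 20% limit is 12.0 mm, and a 465-day tumour reaches 14.4 mm at 24 months. At the ends of the eligible range the pairs are 9.6 and 11.5 mm (8 mm nodule) and 36.0 and 43.1 mm (30 mm nodule).

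**Sections 7 and 8.4 side by side.** A nodule that grows 10% in 2 years is benign under section 8.4, but read literally it does not meet the imaging endpoint of section 7.

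**The case against.** The strongest reply is that the slip errs on the safe side. A reader might infer that it lets slow cancers be labelled benign. At a 24-month CT it does not: a 465-day tumour grows about 44% and is well above 20%. The rule can still be applied as written; only its justification fails. This stands.

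A reader might also infer that patients lost early are counted as benign on a short follow-up. The protocol does not support that as a general statement. Section 8.4 fixes the standard at 24 months, section 9.1(i) excludes patients without diagnosed lung cancer who drop out before 2 years, section 9.1(ii) includes them as censored, and section 5.4 obtains outcomes for those lost to follow-up. What remains is the patient who stays in the study for 2 years but whose 24-month CT was moved earlier or omitted under section 5.2. The wording of the rule does not settle that case, and its frequency is unknown.

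A third inference is that the main limit should simply become 44%. That does not follow. It would place the limit exactly at the growth of the slowest malignancy cited and leave no margin. For short intervals an interval-based limit also falls close to what can be measured: 4.6% at 3 months is 0.46 mm on a 10 mm nodule.

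Finally, section 7 is about the end of participation, and its mention of progression can be read in the light of section 8.4. That is possible but not stated. The protocol has two formulations of the imaging criterion that should agree.

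**Conclusion.** The conversion in section 8.4 is wrong as written, and nothing else in the protocol corrects it or gives another basis for 20%. At 2 years the growth implied by 465 days is about 44%, roughly twice the stated figure; 20% belongs to about 1 year.

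The consequence depends on the last CT. At 24 months the limit is stricter than its rationale. It misses no 465-day tumour, but it withholds the benign label from unbiopsied nodules growing 20% to 44% (doubling times of about 465 to 925 days), for which no label is stated. Applied to a last CT before about 12 months, it is lenient towards a tumour at the cited limit.

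These figures assume exponential growth of a sphere, volume doubling and no measurement error. That the stated figure is wrong does not depend on volume doubling, since the other readings tried also miss 20%. The effect on sensitivity and specificity cannot be quantified, because the protocol gives neither a distribution of growth rates nor the number of nodules that will be judged by imaging alone.

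**What to change.** Before disease status is assigned:

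1. In section 8.4, correct the equivalence (465 days: about 44% at 2 years, about 20% at 1 year), or state that 20% at 24 months is a deliberate margin corresponding to a doubling time of about 925 days.
2. State that size means diameter, and that the 20% limit applies to the 24-month interval and does not by itself establish benign status on materially shorter imaging follow-up.
3. State how an unbiopsied nodule that grows by 20% or more is classified in the accuracy analysis.
4. As a sensitivity analysis only, report sensitivity and specificity with the limit 2^(t/(3 × 465)) − 1, where t is the number of days from baseline CT to last CT.
5. Reconcile the section 7 endpoint with section 8.4.

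All of this concerns the label used in the analysis and leaves biopsy and surveillance decisions untouched. The cost is minor wording and analysis work. Follow-up diameters may have to be extracted from the scan reports sent to the trials unit, because section 5.2 does not list them among the items recorded at follow-up. Some nodules may change label in the sensitivity analysis.
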